## Abstract

**Background:**

Suicide is the leading cause of death among young people. Because it is preventable, suicide prevention has become a critical public health priority worldwide. Current evidence suggests that primary suicide prevention interventions are effective in promoting suicide awareness and reducing suicidal thoughts among adolescents. However, scarce research has been conducted in vulnerable populations who may be at increased risk of suicidal behaviour. This project aims to test the effectiveness of a primary suicide prevention intervention on suicide awareness, knowledge of suicide and local resources, suicidal thoughts, psychological distress, and safety.

**Methods:**

This study is an open-label, multi-centre, superiority, cluster-randomized controlled trial with two parallel arms (randomization 1:1 in at least 8 study sites) of a primary suicide prevention intervention based on psychoeducation versus an art-based control intervention. Four groups of youth aged 14–25 with high suicide risk will be recruited (in total, *n* = 240), including those (1) detained in juvenile detention centres, (2) disconnected from school, (3) in treatment for psychiatric disorders, (4) belonging to a sexual or gender diversity, (5) affected by chronic conditions, and (6) with relational/familial problems. Participants will be randomly assigned to the suicide prevention or control intervention. The primary outcome is suicide awareness measured on a validated scale. Secondary outcomes include knowledge of suicide, knowledge of local resources, suicidal behaviour, psychological distress, access to primary suicide prevention, and safety. Measures will be collected at baseline, at 1-week, and 3-month follow-ups. Analyses will be conducted as intention-to-treat using mixed-effects models.

**Discussion:**

We expect that a brief primary suicide prevention intervention (psychoeducation) will be effective and safe in vulnerable adolescents.

**Trial registration:**

ClinicalTrials.gov NCT06551038. Registered on August 13, 2024.

**Supplementary Information:**

The online version contains supplementary material available at 10.1186/s13063-025-09266-y.

## Introduction

### Background and rationale {6a}

Adolescence, the transition between childhood and adulthood, involves many biological, psychological, and social changes, as well as identity development. It is a crucial period for health behaviours [1] and psychiatric disorders often begin in adolescence [2–4]. Adolescent mental health is therefore increasingly recognized as a public health priority worldwide [1, 5–9]. More specifically, suicide is one of the leading causes of death among young people [10]. Because it is preventable, suicide prevention has become a sustainable development goal in several countries [11, 12]. In addition, many young people who experience suicidal behaviour do not seek professional help [13, 14]. It is therefore important to reach as many young people as possible with primary suicide prevention.

Prevention strategies are usually classified either by the stage of suicidal behaviour (i.e. ‘when’) or by the recipient of the intervention (i.e. ‘who’) [15–17]. On the ‘when’ side, primary prevention occurs before there is any evidence of suicidal behaviour, secondary prevention at early stages (e.g. suicidal ideation) to detect, prevent, and treat, and tertiary prevention after suicidal behaviour has occurred to prevent disability and reduce relapses. Regarding ‘who’ is targeted in suicide prevention research, universal prevention targets the whole population regardless of risk factors, selective prevention targets subgroups at risk of suicidal behaviours, and indicated prevention targets high-risk individuals who have already experienced suicidal behaviour.

Two recent meta-analyses have summarized the evidence on effective strategies for the effectiveness of suicide prevention programmes in adolescents [16, 18]. Overall, the results are encouraging, with suicide prevention interventions reducing suicidal behaviours and psychological distress and increasing suicide awareness and helping skills. However, there are some important research gaps. One of them is the lack of studies conducted among vulnerable populations [16], who are at increased risk of suicidal thoughts and behaviours due to risk factors. Vulnerable adolescents are usually included in selective and indicative prevention, but they may also benefit from interventions such as psychoeducation (suicide awareness) used in primary prevention. This study will test the hypothesis that psychoeducation, which has already demonstrated positive effects on suicidal thoughts and psychological distress in secondary school students, is also effective for vulnerable populations [19]. This is consistent with previous calls to integrate primary and secondary prevention [13] and to include vulnerable youth in suicide prevention research [20].

### Objectives {7}

This study will evaluate the efficacy and safety of a brief primary suicide prevention intervention (i.e. psychoeducation) in vulnerable adolescents.O1: The primary objective is to compare the 1-week efficacy of a brief primary suicide prevention intervention in vulnerable adolescents on suicide awareness.

The study includes seven secondary objectives:

O2: The study will test the 3-month efficacy of a brief primary suicide prevention intervention in vulnerable adolescents on suicide awareness.O3: The study will test the 1-week and 3-month efficacy of a brief primary suicide prevention intervention in vulnerable adolescents on knowledge of suicide.O4: The study will test the 1-week and 3-month efficacy of a brief primary suicide prevention intervention in vulnerable adolescents on knowledge of local resources.O5: The study will test the 1-week and 3-month efficacy of a brief primary suicide prevention intervention in vulnerable adolescents on suicidal thoughts and behaviours.O6: The study will test the 1-week and 3-month efficacy of a brief primary suicide prevention intervention in vulnerable adolescents on psychological distress.O7: The study will explore the proportion of access to primary suicide prevention at baseline in vulnerable adolescents.O8: The study will explore non-response bias.

The study also includes a safety objective, exploring the acceptability and safety (adverse events (AEs) and serious adverse events (SAEs)) of the intervention in vulnerable adolescents.

### Trial design {8}

This is a multi-centre superiority cluster-randomized controlled trial with two parallel arms. Randomization will be 1:1 with stratification on the study sites. Participants will not be blinded regarding their group attribution. The study will include a baseline assessment (*T*_0_), 1-week (*T*_1_), and 3-month (*T*_2_) follow-ups.

## Methods: participants, interventions and outcomes

### Study setting {9}

The study will take place in the French-speaking part of Switzerland. Vulnerable adolescents belonging to the following groups will be recruited for the study: (1) detained in juvenile detention centres, (2) disconnected from school, (3) in treatment for psychiatric disorders, (4) belonging to a sexual or gender diversity, (5) affected by chronic conditions, and (6) with relational/familial problems. The study includes both clinical and community sites (see study sites in Supplementary file 1).

### Eligibility criteria {10}

*Inclusion criteria* are (1) being aged 14 to 25 years old, (2) having good knowledge of French, and (3) signing the informed consent. Exclusion criteria are (1) the medical/educational staff considers that the intervention could interfere with appropriate management of an acute psychiatric disorder or may cause harm to oneself or others and (2) participants are enroled in another suicide prevention intervention during the study period. There is no restriction on the type of therapy or treatment that participants receive.

### Who will take informed consent? {26a}

The adolescent will receive an informed consent form at least 1 week before the intervention. Eligible participants will watch an information video (~5 min in length) that explains the nature of the study, its purpose, the procedures involved, the expected duration, the potential risks and benefits, any inconvenience, the voluntary nature of participation, and the possibility of withdrawing from the study at any time without consequence. The audiovisual material was created by a science filmmaker who successfully developed similar audiovisual material for a previous study [21]. The team member will then answer questions. Adolescents will sign an individual written consent form. Eligible participants who decline to participate will be free to leave or stay and participate in the workshop. The informed consent material can be found in Supplementary File 2.

In this study, we will not seek parental informed consent. Indeed, eligible participants may refuse to participate if their parents need to be involved (e.g. if parents are unaware that eligible participants are engaged in sexual and gender diversity associations) or if parents are not easily available (e.g. in detention centres). Seeking parental consent would lead to excluding the most vulnerable adolescents. However, we will encourage parental information by providing an information sheet for them and offering to answer any questions parents or legal representatives may have. In Switzerland, adolescents can consent to participate in research without the need of parental consent at 14.

### Additional consent provisions for collection and use of participant data and biological specimens {26b}

An additional consent form will be proposed to study participants for the reuse of their data for further research.

### Interventions

#### Explanation for the choice of comparators {6b}

We selected an active control, which matches the experimental intervention in terms of duration, group size, and interactive format. It will help control for non-specific effects such as group participation and attention. The active control was also chosen to avoid potential contamination of the suicide prevention messaging while still providing a meaningful experience for participants, without addressing mental health or suicide.

#### Intervention description {11a}

The framework of the primary suicide prevention intervention under study is psychoeducation. It aims to raise awareness of suicide and provide resources for seeking help for oneself and others [19]. It is delivered by Stop Suicide (www.stopsuicide.ch) and is aimed at young people aged 14 and over. The intervention lasts 90 min and is delivered in groups of 5 to 15 (average 10) participants, with a maximum of 20 to allow for fruitful interaction with all participants. The intervention provides general information about suicidal thoughts and behaviours, information about facts and myths about suicide, identification of risk factors and warning signs of suicidal behaviour, and guidance on how to get help and support for oneself and others within their community. The intervention follows a standardized format, including a lecture, group discussions based on case studies, and a quiz on facts and myths about suicide. The intervention is delivered by a trained Stop Suicide worker supported by a psychologist trained in suicide prevention for children and adolescents. The psychologist is available during and after the intervention. Despite its ‘one size fits all’ approach, the way the intervention is delivered is adapted to the group size, the setting, the age, and the socio-educational level of the young people (e.g. need for language simplification, use of shortened written case examples). A ‘resource person’ from the local team is appointed as the contact person for the participants and Stop Suicide. The resource person is available during and after the intervention on request. Additionally, participants receive a flyer with resources to contact outside their institution in case of psychological distress or suicidal thoughts.

Participants in the control group will receive a non-suicide-related intervention to improve standardization. The control intervention will be an arts-based activity, a workshop on slam poetry. It will be run by the association Slameur.ch, which already offers workshops for vulnerable groups. The duration of the control intervention and number of participants will match those of the intervention group: 90 min in groups of 5 to 15 (average 10) participants, with a maximum of 20 participants. At the end of the intervention, we will give the participants in the control group the same flyer with local resources to contact for suicide prevention. They will therefore receive a low-threshold intervention.

#### Criteria for discontinuation or modification of assigned interventions {11b}

Participants who withdraw from the study will not be replaced. They are free to discontinue participation at any time and for any reason. Participants are considered to have withdrawn if they leave the study before completion or are lost to both follow-ups. If the study team has no news of a participant, we will try to contact them to find out the reason for dropping out. If a participant withdraws due to an AE, the study team will try to collect information. The sample size calculation takes into account attrition (20%). All participants will be analysed in their original study group (i.e. intention-to-treat analyses), and all available data up to the discontinuation will be used.

#### Strategies to improve adherence to interventions {11c}

To improve study retention and encourage participation [22], we will use compensation and train the study team to search for and contact participants who have dropped out [23]. Participants who do not attend the follow-up assessment will be contacted to complete it. To avoid attrition, we plan to have a short-term primary outcome. Short-term follow-up of vulnerable populations has been described as feasible, so a 1-week follow-up is reasonable [24]. Attrition at the cluster level is not expected. For the secondary outcome at 3 months, we will contact participants by telephone. To avoid attrition, we will ask for contact details (e.g. phone number, email, postal address, phone number of a parent or caregiver). We will ask participants for their preferred means of communication and offer the use of social media (e.g. Snapchat, TikTok).

The interviewers will encourage participants to answer all missing questions on self-report instruments. The analysis strategy will help to deal with missing data by integrating multiple imputation methods.

To avoid contamination (i.e. the intervention group sharing suicide prevention information with the control group), we will plan to assess the groups at different time points. As in most settings, adolescents do not remain for extended periods; the risk of contamination bias is low. Routine care may vary between study sites. It will be adequately recorded and described for each site and included as a covariate in the models. Standardized staff training on suicidal behaviour management and suicide prevention will improve the comparability of responses to suicidal behaviour between sites. The potential effect on participants will be the same in both groups (intervention and control), so there will be no bias in conclusions about the benefits of the intervention.

#### Relevant concomitant care permitted or prohibited during the trial {11d}

Not applicable.

#### Provisions for post-trial care {30}

In the context of the ESPAIR trial, no post-trial provisions are planned. Participants will continue to have access to usual care and services provided by their respective site staff.

### Outcomes {12}

#### Nine-item perceived suicide awareness scale (PSAS-9) [25] (O1–O2)

We will use a composite measure of suicide awareness, one of the most recurring outcomes for suicide prevention programmes [19]. The PSAS-9 comprises perceived knowledge about suicide, confidence, and willingness to talk about suicide and seek help [25]. This measure is distinct from objective knowledge about suicide, which is often used as an outcome for suicide prevention programme evaluation and a proxy of suicide literacy [25]. Suicide awareness focuses on self-efficacy, a different dimension of suicide awareness that concentrates on one individual’s confidence in their ability to adopt a behaviour according to social cognitive theory [26]. The PSAS-9 was developed using a questionnaire from a suicide prevention study [25] and has already been successfully validated and used in secondary schools in Switzerland [19, 27]. Psychometric properties were acceptable (Cronbach alpha = 0.78, correlation for test-retest = 0.68, factor analyses suggesting the suitability of a one-factor model). Items are scored on a five-point scale (ranging from 0 = strongly disagree to 4 = strongly agree). A sum score of the nine questions (range 0–36) will be calculated. The final score at *T*_1_ will be used as the primary outcome (O1), while the final score at *T*_2_ will be a secondary outcome (O2).

#### Literacy of suicide scale (LOSS) [28] (O3)

The LOSS tests knowledge about suicide and its risks using 12 questions with true/false responses. The LOSS is often successfully used in suicide prevention research [29] and available in French [28]. We will compute a total score of correct responses (range 0–12). Knowledge on suicide will be assessed at *T*_0_, *T*_1_, and *T*_2_. The final scores at *T*_1_ and *T*_2_ will be used as secondary outcomes.

#### Knowledge of local resources (O4)

A questionnaire on knowledge about local resources has been developed for the project’s purpose. Five questions measured on a five-point scale (ranging from 0 = strongly disagree to 4 = strongly agree) will be used to assess whether adolescents are aware of locally available resources when they need help with suicidal behaviour. A sum score of true responses (range 0–20) will be computed. Knowledge of local resources will be assessed at *T*_0_, *T*_1_, and *T*_2_. The final scores at *T*_1_ and *T*_2_ will be used as secondary outcomes.

#### Suicidal ideation attributes scale (SIDAS) [30, 31] (O5)

This five-item measure, scored on a 0–10 scale, is designed to identify the presence and severity of suicidal thoughts. It has excellent psychometric properties and is available in French [30, 31]. A sum score ranging from 0 to 50 is computed. Suicidal ideation will be assessed at *T*_0_, *T*_1_, and *T*_2_. The final scores at *T*_1_ and *T*_2_ will be used as secondary outcomes.

#### Kessler psychological distress scale (K-6) [32, 33] (O6)

The K-6 estimates global psychological distress over the previous 4 weeks [32, 33]. This six-item measure is assessed on a five-point scale (range 0–4) and has strong psychometric properties. A French version is available. A sum score ranging from 0 to 24 is computed. Psychological distress will be assessed at *T*_0_, *T*_1_, and *T*_2_. The final scores at *T*_1_ and *T*_2_ will be used as secondary outcomes.

#### Access to primary suicide prevention (O7)

Previous access to primary suicide prevention will be assessed using three questions derived from an earlier study [34] and developed with the support of the Swiss Centre of Expertise in the Social Sciences. Participants will be asked whether they have received primary suicide prevention training in the past, including workshops, low-threshold prevention (e.g. videos, flyers), and whether they have sought information on their own (e.g. Internet, social network, family or peers). Each question will be coded as a categorical variable with three response options (‘Yes, within the past 12 months’; ‘Yes, more than 12 months ago’; ‘No’) and reported as a proportion of participants in each category. Access to primary suicide prevention will be assessed at T_0._

#### Attrition (O8)

Attrition will be coded as 1 if participants drop out of the study (drop out after *T*_0_ measure or *T*_0_ and *T*_1_ measures) and 0 if they remain in the study until the end. Attrition will be assessed as a proportion per group after *T*_2_.

#### Safety outcomes

We will systematically record SAEs, including suicide attempts and deaths by suicide before the participants leave the study site and up to 1-month post-baseline. According to the Swiss legislation, a SAE is any adverse event that [1] results in death or is life-threatening, (2) requires inpatient hospitalization or prolongation of existing hospitalization, (3) results in persistent or significant disability or incapacity, or (4) results in a congenital anomaly or birth defect. An in-depth clinical assessment by psychiatrists with an expertise in suicidal behaviours will be conducted in case of suicide attempts or deaths by suicide to rule out or establish a possible link to the intervention. Other AEs include self-harming, insomnia, appetite problems, substance use, and para-suicidal endangerment behaviours, as identified and reported by the local team before the participants leave the study site and up to 1-month post-baseline. Proportions of participants with the respective (S)AEs will be reported. At T_1_, we will also record self-reported distress due to the intervention using two questions related to the distressing and pleasurable nature of the intervention on a scale from 0 to 4 [19, 25]. We will use a sum score at *T*_1_ as the safety outcome.

In addition, we will collect the relevant following characteristics at T_0_:

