#### Sociodemographic variables

We will register age (in years), parental level of education using mother and father’s job, region of origin (Swiss cantons and foreign countries), and migration status (type of residence permit). We will also ask participants whether they belong to a gender or sexual minority. We will use the Gender-Role Identity Scale (GRIS) [35], which has been validated in French. The GRIS uses 11 questions and covers three dimensions: sex assigned at birth and gender identity (questions 1 to 4, categorical items, will be reported as proportions), sexual orientation (item 5, will be reported as proportion), and gender roles and identity (questions 6 to 11, items 6 to 8 capturing masculinity and 9 to 11 femininity, combined into a single score ranging from − 2 (very feminine) to + 2 (very masculine), will be reported as mean scores) [35].

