#### Safety

We will calculate the percentage of SAEs, attempted suicides, and deaths by suicide separately in each group, with 95% confidence intervals. As the number of events will presumably be very low, no inferential test is planned. We will also use percentages with 95% confidence intervals for AEs. We will calculate mean scores of self-reported acceptability using standardized mean differences between the intervention and control groups.

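### The self-reported safety score sums a distress item and a pleasure item with no stated direction, so it does not isolate distress; the distress item should be reported on its own

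*Protocol article*

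**What the plan says.** In the protocol article, Outcomes {12}, Safety outcomes, the construct is named as distress: "we will also record self-reported distress due to the intervention using two questions". The items are "two questions related to the distressing and pleasurable nature of the intervention on a scale from 0 to 4". The scoring rule follows: "We will use a sum score at *T*_1_ as the safety outcome". The section gives no range for this sum, does not say which end is worse, and does not say whether either item is reversed.

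The Safety paragraph under Statistical methods gives the analysis: "We will calculate mean scores of self-reported acceptability using standardized mean differences between the intervention and control groups". No other acceptability measure is defined in the article, so this appears to be the same two-item score under another name. Nowhere is the distress item planned to be shown by itself.

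Three other statements bear on the point:

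- Objectives {7} treats the two ideas as one exploratory aim: "The study also includes a safety objective, exploring the acceptability and safety".
- Intervention description {11a} fixes the comparator: "The control intervention will be an arts-based activity, a workshop on slam poetry".
- Adverse events are handled separately from the score: "Proportions of participants with the respective (S)AEs will be reported".

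**The concern.** The two items point in opposite directions. Added as they stand, they give a total whose high end has no clear meaning: the maximum of 8 belongs to someone who found the session both very distressing and very pleasurable. A difference between arms on that total is the distress difference plus the pleasure difference, so a rise in one and a fall in the other offset.

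The design makes such a pattern plausible, since a session about suicide is compared with a creative workshop. The safety objective concerns young people described as at high risk. Among the designated safety outcomes, this score is the only one that participants report themselves and the only one that asks about distress caused by the workshop. A reader shown a standardized difference near zero could not tell whether distress was the same in both arms or whether higher distress had been masked by lower enjoyment.

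Reversing the pleasure item removes the cancellation but leaves a second problem. The total then treats a dull session as a harmful one, and the article's two names for the score, distress and acceptability, are not the same thing.

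**Working it through.** The article gives no expected value, SD or effect size for this score, so there is no figure to reproduce. The check enumerates the score and then works through assumed scenarios.

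**Inputs from the article:** two items, D (distressing) and P (pleasurable), each 0 to 4; scoring by sum.

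**Step 1. Single participants.** Literal sum = D + P. Sum with pleasure reversed = D + (4 − P). Both run from 0 to 8.

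| D | P | D + P | D + 4 − P |
|---|---|---|---|
| 4 | 0 | 4 | 8 |
| 3 | 1 | 4 | 6 |
| 2 | 2 | 4 | 4 |
| 1 | 3 | 4 | 2 |
| 0 | 4 | 4 | 0 |
| 4 | 4 | 8 | 4 |
| 0 | 0 | 0 | 4 |

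The first five rows run from the worst experience to the best. The literal sum gives all of them 4; the reversed sum separates them.

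**Step 2. Difference between arms.** Assumptions, not from the article: each item has SD 1, the intervention raises distress by 0.5, pleasure falls by c, and the two items correlate at r between −0.6 and +0.3.

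- Literal sum: SMD = (0.5 − c) / √(2 + 2r)
- Reversed sum: SMD = (0.5 + c) / √(2 − 2r)

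| Fall in pleasure, c | Literal sum, range over r | Reversed sum, range over r |
|---|---|---|
| 0 | 0.31 to 0.56 | 0.28 to 0.42 |
| 0.25 | 0.16 to 0.28 | 0.42 to 0.63 |
| 0.5 | 0 | 0.56 to 0.85 |

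Example at r = −0.6, c = 0.25: literal 0.25 / √0.8 = 0.28; reversed 0.75 / √3.2 = 0.42. The distress item alone gives 0.5 in every row.

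**Step 3. No distress difference, less enjoyment.** Set the distress shift to 0 and c to 0.5, under the same assumptions.

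- Reversed sum: 0.5 / √(2 − 2r) = 0.5 / √3.2 = 0.28 at r = −0.6, and 0.5 / √1.4 = 0.42 at r = +0.3. The intervention looks less safe although it distressed nobody more.
- Literal sum: −0.5 / √(2 + 2r), that is −0.56 to −0.31. If high is read as worse, the intervention looks safer because it was less enjoyable.

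**Step 4. Comparison within the article.** For the gender-role scale in Sociodemographic variables, which also joins opposed items, the article does fix the meaning: the items are "combined into a single score ranging from" −2 (very feminine) to +2 (very masculine). The safety score has no such statement.

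**The case against.** The strongest reply is that the missing reverse-coding is inferred from silence. The article names the construct as distress and says that both questions measure it, which fits reversing the pleasure item. The items are cited to earlier studies, the case report form is available only on request, and item keying could sit in the full protocol or the analysis plan. The article does not spell out item reversal for its other sum scores either. This stands: a reader might infer that the two items will cancel and that the score cannot show distress, but the article does not establish that. Even on the literal sum, cancellation is complete only when the shifts are equal and opposite; if pleasure does not change, the distress signal comes through.

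A reader might also infer that the plan would support a false declaration of safety. That does not follow. Adverse and serious adverse events are reported separately with 95% confidence intervals. Suicidal ideation (SIDAS) and psychological distress (K-6) are self-reported at every visit and compared between arms with mixed models. The score itself carries no planned test, and no primary or secondary efficacy analysis depends on it.

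Two things limit this reply. First, SIDAS and K-6 are efficacy outcomes that do not ask about the workshop. K-6 looks back 4 weeks, so at 1 week about 4 − 1 = 3 weeks of its window precede the session. Second, the charitable reading does not repair the composite: Step 3 of the working shows that a correctly reversed sum still registers low enjoyment as harm. Pairing acceptability with safety in one objective does not require adding them into one number.

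**Conclusion.** The point holds in a limited form. The article defines its self-reported safety outcome as a sum of two items of opposite valence, leaves direction, range and reversal unstated, and apparently calls the same score distress in one section and acceptability in another. Neither possible keying gives a clean measure of distress. Unreversed, opposing shifts offset partly, or fully if equal; reversed, low enjoyment and harm are mixed.

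The sizes rest on assumed item SDs, shifts and correlations, since the article gives none. With a distress difference of 0.5 SD and pleasure falling by between 0 and 0.5 SD, the literal sum ranges from 0.56 down to 0 and the reversed sum from 0.28 to 0.85. The identification of the acceptability score with the two-item sum is also an inference, though no other candidate is defined.

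Because the measure is descriptive and one of several sources on harm, the severity is moderate to minor. It does not need to be resolved before the trial can proceed.

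**What to change.** In Safety outcomes, name the distress item alone as the self-reported safety outcome at 1 week, and name the pleasure item separately as acceptability. In the Safety paragraph of the statistical methods, report for the distress item the mean in each arm, the difference with a 95% confidence interval that allows for clustering, and the distribution of responses from 0 to 4 by arm. Report the pleasure item in its own line.

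If a sum is kept for comparison with earlier studies, reverse-code the pleasure item, state the range (0 to 8) and that higher is worse, use one construct name in both sections, and still show the two items separately.

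The cost is a few sentences in the protocol and analysis plan. Both items are already collected, so there is no change to the questionnaire, the visits or the sample size.
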